# The effect of a clinical decision-making mHealth support system on maternal and neonatal mortality and morbidity in Ghana: study protocol for a cluster randomized controlled trial

**DOI:** 10.1186/s13063-017-1897-4

**Published:** 2017-04-04

**Keywords:** Maternal, Neonatal, Clinical decision-making, Mobile health (mHealth), Text messaging, Ghana

## Abstract

**Background:**

Mobile health (mHealth) presents one of the potential solutions to maximize health worker impact and efficiency in an effort to reach the Sustainable Development Goals 3.1 and 3.2, particularly in sub-Saharan African countries. Poor-quality clinical decision-making is known to be associated with poor pregnancy and birth outcomes. This study aims to assess the effect of a clinical decision-making support system (CDMSS) directed at frontline health care providers on neonatal and maternal health outcomes.

**Methods/design:**

A cluster randomized controlled trial will be conducted in 16 eligible districts (clusters) in the Eastern Region of Ghana to assess the effect of an mHealth CDMSS for maternal and neonatal health care services on maternal and neonatal outcomes. The CDMSS intervention consists of an Unstructured Supplementary Service Data (USSD)-based text messaging of standard emergency obstetric and neonatal protocols to providers on their request. The primary outcome of the intervention is the incidence of institutional neonatal mortality. Outcomes will be assessed through an analysis of data on maternal and neonatal morbidity and mortality extracted from the District Health Information Management System-2 (DHIMS-2) and health facility-based records. The quality of maternal and neonatal health care will be assessed in two purposively selected clusters from each study arm.

**Discussion:**

In this trial the effect of a mobile CDMSS on institutional maternal and neonatal health outcomes will be evaluated to generate evidence-based recommendations for the use of mobile CDMSS in Ghana and other West African countries.

**Trial registration:**

ClinicalTrials.gov, identifier: NCT02468310. Registered on 7 September 2015; Pan African Clinical Trials Registry, identifier: PACTR20151200109073. Registered on 9 December 2015 retrospectively from trial start date.

**Electronic supplementary material:**

The online version of this article (doi:10.1186/s13063-017-1897-4) contains supplementary material, which is available to authorized users.

## Background

The era of the Millennium Development Goals (MDGs) has shown that with appropriate strategies and political will, millions of lives can be improved and saved worldwide [1, 2]. Maternal deaths were halved and under-5 mortality rate (U5MR) declined by more than half over the 25 years of the MDGs [1]. Despite this success, maternal, neonatal and child health care remains a prominent public health concern, particularly in sub-Saharan Africa and Southern Asia where most countries did not attain MDGs 4 and 5 [2–5]. About 13.6 million women are estimated to have died globally from maternal causes between 1990–2015 [2]. An estimated 303,000 of these deaths occurred in 2015; 99% of them occurred in low-and- middle income countries (LMIC) and 66% in sub-Saharan Africa (SSA). Neonatal deaths also accounted for 40% of the eight million childhood deaths in 2010 [6–8]. Ninety-eight percent of these neonatal deaths occurred in LMIC. Though there is evidence of accelerating decline in maternal and U5MR in all regions of the world [2, 3, 9, 10] the rate of decline is uneven among countries [2, 11]. Inequalities still exist in birth outcomes for mothers and their babies globally; the lifetime risk of a woman dying from maternal causes in SSA is 1 in 36 as compared to a lifetime risk of 1 in 4900 in high-income countries (HIC) [2]; neonates born in SSA are six times more likely to die compared to neonates born in HIC [12]. With regards to the decline of U5MR, particularly in the early neonatal period only minor declines have been achieved [9, 11]. It is projected that the global composition of U5MR will continue to shift towards a younger age structure, and that if decreases in child mortality do not focus on neonatal deaths, neonatal deaths will account for about 44.9% of under-5 mortality by 2030 [3].

Maternal and neonatal deaths are caused by a complex interaction of economic, financial, social, cultural and clinical factors [13]. Clinical factors are related to access and quality of antenatal care, skilled attendance at delivery, emergency obstetric care services and postnatal care for neonates. Gaps identified in the quality of care (QOC) given to pregnant women and their newborns include poor quality of clinical decision-making by health providers. Besides knowledge acquired during education in professional training institutions, health providers are known to rely on past experiences, tacit knowledge and intuition, referred to as “mind-lines” [14, 15], in making clinical decisions for their patients. Different categories of frontline providers deliver maternal and neonatal services within and across various health facilities and as such their experiences, intuitiveness and ability to learn from colleagues may vary as shown in differences in risk-taking preferences and attitude towards risk which can lead to significant variations in the way that decisions regarding patient care are made [16]. Reliance on these mind-lines may not be based on empirical evidence, and may affect the QOC rendered to clients. These mind-lines, therefore, cannot be depended upon for sustained QOC which is needed to reduce maternal and neonatal morbidity and mortality.

The use of information and communication technology (ICT) in the form of mobile phones, commonly referred to as mHealth, provides potentially important tools to maximize health worker impact and efficiency [17, 18] and improve service utilization [19] as global efforts to improve maternal, neonatal and child health care intensifies through the Sustainable Development Goals (SDGs) 3.1 and 3.2 already underway [20]. Generally, mHealth interventions are well received by health workers and the community [21]; however, data is limited as to their effectiveness on patient outcomes, efficiency of health systems or their use by health workers [17, 19, 21–24]. Major areas of application of mHealth interventions has been in the area of tools and communication to support health workers, adherence to treatment regime and data collection [21, 23]. Positive evidence for the applicability of mHealth solutions suggest that mobile phones can contribute in reducing the various phases of delay in obtaining help for pregnant women, reducing program cost and improving correct management of patients when used as a decision-making tool [17, 21, 22, 25]. As mobile phone penetration is high even in remote areas in SSA [17] their use by health workers to deliver health care is feasible irrespective of prior education or training in their use [21, 24].

Ghana, a SSA country, is one of the 26 countries whose U5MR contributed to 80% of the world’s childhood mortality in 2013 [3]. The neonatal mortality rate is 29 deaths per 1000 live births with higher mortality rates being reported in rural areas of the country [26–28]. Ghana’s maternal mortality is presently estimated at 319 per 100,000 live births [29]. Clinical causes of persistently high maternal and neonatal mortality identified in Ghana include nonadherence of health workers to clinical guidelines [30, 31]. Though the prevalence of antenatal clinic (ANC) attendance among pregnant women is high in Ghana, skilled attendance at birth is not optimal (about 74%) [27, 32]. Notable barriers to accessing skilled attendance at birth in Ghana include cost, distance, availability of health facilities and attitudes of nurses towards pregnant women [32, 33]. The importance of the QOC given to pregnant women and their newborns for those who opt for skilled attendance at delivery, can therefore not be understated.

To help reduce maternal and neonatal mortality in Ghana, we designed an mHealth intervention – a clinical decision-making support system (CDMSS) facilitating easy access to maternal and neonatal guidelines for routine and emergency obstetric, antenatal and neonatal care for frontline providers of maternal and neonatal care in Ghana. Our main study objective is to assess the effect of CDMSS on the incidence of health facility-based neonatal and maternal mortality.

## Methods/design

### Study design

A cluster randomized controlled trial (CRCT) to evaluate the effect of a mobile clinical decision-making support system on maternal and neonatal mortality and morbidity will be conducted in 16 districts in the Eastern Region (ER) of Ghana. This study will comprise three components: (1) a baseline study to assess the characteristics of the health facilities and outcome measures of interest in study sites, (2) implementation of a CDMSS for 18 months and (3) a sub-study to assess the QOC of maternal and neonatal care services at baseline and at the end of the study.

### Study site

The study will be conducted in the ER of Ghana. The ER is the sixth largest region in terms of land area in Ghana (Fig. 1). With an estimated mid-year population of approximately 2.5 million, which is10.7% of the total national population [34], the ER is the third most populous region in Ghana. The region consists of 21 administrative districts with Koforidua in the New Juaben district as its regional capital. The ER is predominately rural in nature with pockets of urban areas in mainly the district capitals. About 40% of its inhabitants reside in 4 out of its 21 administrative districts. The most populous districts are Afram Plains Kwahu North district, West Akim district, Kwaebibirem and New Juaben district in descending order. Agricultural (mainly fish and crop farming) and mining activities are the main stay of economic activities of the region. The estimated growth rate of the ER is 2.0% [35].

**Fig. 1 Fig1:**
[figure not shown]
Map of districts in the Eastern Region of Ghana. The districts were defined as cluster units. Sixteen districts fulfilled our inclusion/exclusion criteria. The regional capital, New Juaben Municipal, was excluded from the sampling to avoid selection bias as its regional hospital serves as the highest referral point in the region

Each district comprises a number of subdistricts that form the administrative health subdistricts for the region. There are a total of 250 health facilities, including 31 hospitals in the region, that serve the health needs of the region’s populace [35]. Like other parts of the country, the main categories of health care facilities in the ER are – Community-based Health Planning and Services (CHPS), health centres (HC) and maternity homes and hospitals. At the primary health care level, the CHPS, HC and maternity homes provide services, including maternal and neonatal health services, to the various communities and refer cases to the hospitals. The regional neonatal mortality rate (NMR) was 29 per 1000 live births in 2008 [28]. From 2004 to 2014 the NMR of the ER was estimated as 30 per 1000 live births, showing little change over the period [27]. Presently, the ER ranks sixth in terms of high NMR in Ghana [27]. The pregnancy-related mortality ratio was also 594 per 100,000 live births in 2007 [36]. The ER was selected for this study for two reasons: its high neonatal and maternal mortality rates and because the intervention could not be implemented in the Greater Accra region where it had been designed and piloted [37].

### Cluster selection criteria

The inclusion criteria for cluster selection for this study include the following: (1) The district is located in the ER, (2) The district has expected deliveries of at least 1100/year for the year 2014, (3) The District Health Management Team and the District Hospital Management Team agree to participate in the study and (4) Health facilities within the district conducted at least one delivery in the year 2014. The exclusion criteria for our study are: (1) The district is located outside the ER, (2) The district has expected deliveries of fewer than 1100/year for the year 2014, (3) The District Health Management Team and the Hospital Management Team do not agree to participate in the study and (4) Health facilities within the districts have not conducted at least one delivery during the year 2014.

The year 2014 was selected as the baseline year as the most current data pertaining to deliveries (births) at the time of commencement of the study was for that year. A delivery (births) was a criterion for recruitment as most obstetric and neonatal complications occur around childbirth. Intervention during this period is crucial for survival and health [38].

### Sample size estimation

This study is a superiority trial and has been designed and powered for neonatal mortality to contribute evidence for improved neonatal health care considering the predicted global upward trend in neonatal deaths [3] compared to maternal deaths. Two formulae were applied; the first formula was applied to estimate the required sample size in a randomized controlled trial (RCT) with binary outcome while the second formula was applied to inflate the estimated sample size for a CRCT. Neonatal mortality is the primary outcome, and is currently at approximately 30/1000 live births in the ER, Ghana. Evidence from previous studies including systematic reviews focusing on neonatal care interventions have shown a 23% to 51% reduction in neonatal mortality in settings including LIMC [39–44]. Our intervention will also address neonatal and maternal health care, hence we estimate an effect size of 30% on neonatal mortality with the use of this intervention. Intracluster correlation coefficient (ICC) for neonatal mortality in Ghana has been estimated at 0.0007256 [45]. To detect a 30% decline in neonatal mortality at a power of 80%, a significance level of 0.05 (two-tailed test), with a fixed number of eight clusters in each arm of the study, approximately 1065 patients in each of the 16 clusters will be needed. The first formula is:$$ m=\frac{n\left(1-\rho \right)}{\left( k- n\rho \right)}, $$where *m* = number of patients per cluster, *k* = number of clusters in each arms of the study, *ρ* = ICC and *n* = is the number of patients needed to detect this effect in a RCT. The second formula is:$$ n\kern0.5em =\kern0.5em \theta \left[\frac{\pi_{{}_{\mathbf{1}}}\left(1-{\pi}_{\mathbf{1}}\right)\kern0.5em +\kern0.5em {\pi}_{\circ}\left(1-{\pi}_{\circ}\right)}{{\left({\pi}_{\mathbf{1}}-{\pi}_{\circ}\right)}^2}\right] $$where *π*
_1_ = is the expected proportion of the neonatal mortality at the intervention group after RCT, *π*∘ = is the expected proportion of the neonatal mortality at the reference group after RCT and ϴ is the variance of the two proportions at a power of 80% and significance level of 0.05.

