## Outcome measures

Institutional neonatal mortality will be considered as the primary outcome measure for this study. For this study neonatal mortality is defined as death of a newborn occurring from birth up to the 28th day of life [12]. Multiple secondary outcome measures pertaining to maternal and neonatal outcomes will also be measured. Aggregate data on primary and secondary outcomes will be extracted from (DHIMS-2) and health facility health record books for non-hospital facilities (Table 1).

**Table 1 Tab1:** Data sources for outcome measures

Outcome measure	Source of data			
	Hospital	Health centre	CHPS	Maternity home
Number of cases of birth asphyxia	DHIMS-2	Facility	Facility	Facility
Number of cases of low birthweight	DHIMS-2	Facility	Facility	Facility
Number of cases of neonatal jaundice	DHIMS-2	Facility	Facility	Facility
Number of cases of neonatal sepsis^a^	DHIMS-2	Facility	Facility	Facility
Number of cases of PIH/pre-eclampsia/eclampsia	DHIMS-2	Facility	Facility	Facility
Number of cases of postpartum hemorrhage	DHIMS-2	Facility	Facility	Facility
Number of cases of prolonged labor	DHIMS-2	Facility	Facility	Facility
Number of cases of puerperal sepsis	DHIMS-2	Facility	Facility	Facility
Number of cases of neonatal deaths	DHIMS-2	Facility	Facility	Facility
Number of cases of maternal deaths	DHIMS-2	DHIMS-2	DHIMS-2	DHIMS-2
Total number of deliveries	DHIMS-2	DHIMS-2	DHIMS-2	DHIMS-2
Total number of ANC attendants	DHIMS-2	DHIMS-2	DHIMS-2	DHIMS-2

^a^Cord sepsis used as a proxy for neonatal sepsis in this study; *ANC* antenatal clinic, *CHPS* Community-based Health Planning and Services, *DHIMS-2* District Health Information Management System-2, *PIH* pregnancy-induced hypertension

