Though this study will provide much needed evidence to bridge the knowledge gap about the effect of mHealth intervention on maternal and neonatal health outcomes, the study has some limitations. Firstly, we assume that once the USSD platform is assessed, the information retrieved will be used for action; this may not always be the case. We expect that the assessment of the QOC of maternal and neonatal health care services in the four purposively selected clusters will address this limitation to a large extent. Secondly, there is generally a limitation with regard to network availability, electricity and well-functioning phones in Ghana, particularly in the rural areas; this may affect the ability of health care providers in some remote areas to use the intervention. Thirdly, this study will not assess neonatal or maternal mortality at the community level. The attributable risk of death for neonates born at home compared to those born in health facilities in SSA is estimated to be 21% [53]. The DHIMS-2 database from which data for evaluation of the CRCT will be extracted is a web-based platform built on the District Health Information System-2 (DHIMS-2) open source software. DHIMS-2 serves as a data recording, collection, collation and analysis tool that hosts the entire national health data of Ghana. Data entry into the DHIMS-2 is done using primary data collection tools and standard registers designed for various health services and programs. The DHIMS-2 does not capture community-level health outcomes. The contribution of out-of-facility deaths to maternal and neonatal mortality is, therefore, not captured in the DHIMS-2. The CDMSS has also been implemented as an institutional-based support system to be used by health facilities that contribute data to the DHIMS-2. Thus, community-level data (contribution of the out-of-health facility deliveries to neonatal and maternal deaths) will not be assessed in this study. However, given that 74% of deliveries in Ghana occur in a health facility with a skilled attendant [27], we expect our sample to include the majority of maternal and neonatal clients because clients who self-select to deliver at health facilities are usually followed up in the communities by the health workers. These clients are likely to seek health care services from these facilities. Lastly, there may be concurrent maternal and neonatal health care interventions running at the time of the trial. These interventions could influence the results of our study although they are likely to be independent from the randomization. However, the study team will document all concurrent maternal and neonatal health services occurring in the study sites and carefully interpret our results based on this real-life context.

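### The 80% power and 1065 per cluster are calculated from a region-wide neonatal death rate, while the primary outcome counts only deaths recorded in facilities, so the stated power is not established for that outcome

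*Protocol article*

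**What the plan says.** Under Sample size estimation the protocol article states: "Neonatal mortality is the primary outcome, and is currently at approximately 30/1000 live births in the ER, Ghana". It then assumes a 30% reduction, an intracluster correlation (ICC) of 0.0007256, two-sided 5% significance, 80% power and eight clusters per arm, and arrives at about 1065 patients per cluster. The Study site section shows where the rate comes from: "From 2004 to 2014 the NMR of the ER was estimated as 30 per 1000 live births, showing little change over the period".

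The outcome to be analysed is narrower. Under Outcome measures: "Institutional neonatal mortality will be considered as the primary outcome measure for this study". The window runs to day 28 ("neonatal mortality is defined as death of a newborn occurring from birth up to the 28th day of life"), and Table 1 takes the deaths from DHIMS-2 for hospitals and from facility records elsewhere. The limitations in the Discussion add: "The contribution of out-of-facility deaths to maternal and neonatal mortality is, therefore, not captured in the DHIMS-2".

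The Discussion softens this by noting "given that 74% of deliveries in Ghana occur in a health facility with a skilled attendant" and by expecting these clients to be followed up and to return to the facilities. It does not connect the limitation to the power calculation.

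**The concern.** The regional rate covers all live births and all deaths to day 28, wherever they occur. The trial's outcome covers deaths that a participating facility records. A baby born in a facility who dies at home after discharge is a death in the first quantity and, as far as the document shows, not in the second. The design rate and the analysed outcome therefore differ, and no adjustment is described.

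The 80% power and the 1065 are stated properties of the trial. If the institutional rate is lower, the same design has less power for the same relative effect, and a null result could be taken as stronger evidence against a 30% reduction than the trial can supply.

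The ICC raises a smaller question. Sample size estimation gives it for neonatal mortality in Ghana without saying whether it describes community or facility deaths.

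**Working it through.** **Inputs.** Control rate 0.030, 30% reduction (so 0.021), ICC ρ = 0.0007256, k = 8 per arm, two-sided 5%, 80% power (Sample size estimation). At least 1100 expected deliveries per district per year (Cluster selection criteria). 18 months of implementation (Study design). 74% of deliveries in facilities in Ghana, and a 21% attributable risk for home against facility birth in sub-Saharan Africa (Discussion).

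**1. The plan's own figure.** θ = (1.960 + 0.842)² = 7.849.
n = 7.849 × (0.021 × 0.979 + 0.030 × 0.970) / 0.009² = 4,812.
m = n(1 − ρ)/(k − nρ) = 4,808.5 / (8 − 3.4915) = 1,066.5, against 1065 stated. This reproduces. With 0.029 as the control rate, m is 1,135, so the stated size does rest on 30/1000.

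**2. What the document's own figures imply for facility births.** If 74% of births are in facilities and the 21% is read as the home-versus-facility excess, the rate among facility-born babies is 30/(0.74 + 0.26/0.79) = 28.1 or 30/(0.74 + 0.26 × 1.21) = 28.4 per 1000, depending on how the 21% is defined. This adjusts only for place of birth. It still counts every death to day 28, including deaths at home after discharge, whose share is not given.

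**3. Reading other rates.** If facilities record a share s of all neonatal deaths and hold 74% of births, the institutional rate is 30 × s/0.74 per 1000. It equals 30 only if s = 74%. It is 28.4 at s = 70% and 20.3 at s = 50%. The document does not give s.

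**4. Power at other rates.** Power = Φ(0.3p/SE − 1.960), with SE² = [p(1 − p) + 0.7p(1 − 0.7p)] × DE/(8m) and DE = 1 + (m − 1)ρ. The low end keeps ρ = 0.0007256. The high end keeps the between-cluster coefficient of variation (CV) implied at 30/1000: CV² = 0.0007256 × 0.970/0.030 = 0.02346, so CV = 0.153, and ρ = CV² × p/(1 − p).

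Example at 20/1000 and 1065 per cluster, same ICC: DE = 1 + 1064 × 0.0007256 = 1.772; 8 × 1065/1.772 = 4,808; SE = √(0.033404/4,808) = 0.002636; 0.006/0.002636 − 1.960 = 0.316; power 62%. Same CV: ρ = 0.000479, DE = 1.510, SE = 0.002433, power 69%.

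The second column of results uses 1100 × 1.5 × 0.74 = 1,221 births per cluster, an assumed facility yield at the eligibility minimum.

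| Assumed institutional rate per 1000 facility births | Power, 1065 per cluster | Power, 1,221 per cluster |
|---|---|---|
| 28 | 77–78% | 80–81% |
| 25 | 72–76% | 75–79% |
| 20 | 62–69% | 66–73% |
| 15 | 50–61% | 53–65% |

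A higher institutional rate would raise power: 35/1000 gives 86% at 1065 per cluster with the same ICC.

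**The case against.** The strongest reply is that the loss may be small. The document's only relevant figures give about 28/1000 and 77–78% power. The 1065 is a requirement and not a cap: 18 months in districts with at least 1100 expected deliveries a year may yield more births, and at 1,221 per cluster the 80% is recovered at 28/1000. Restricting to facilities narrows the denominator as well as the numerator, and referral of sick newborns into hospitals could raise the recorded rate. Non-capture is disclosed as a limitation, and results will carry 95% confidence intervals, which limits misreading of a null.

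All of this bears on size and stands as such. It does not supply the missing link between the regional rate and the institutional outcome. The 28/1000 is not an institutional rate, because it leaves out the loss of deaths after discharge. The expectation that clients return to facilities is not quantified. As for referral, the region's highest referral hospital lies in the excluded district, so some referred deaths may fall outside the 16 clusters.

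A reader might infer three stronger conclusions, none of which the document supports:

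- **Power is probably far below 80%.** At 1065 per cluster that needs an institutional rate of about 20/1000 or less, which the document neither gives nor excludes.
- **The target becomes unreachable.** At the fixed ICC no cluster size reaches 80% below about 13.3/1000. But holding the ICC fixed down to 10/1000 implies that the between-cluster CV rises from 0.153 to 0.268. With the CV held at 0.153, a solution exists at 10/1000 (3,252 per cluster).
- **The ICC belongs to the wrong outcome.** It rests on a cited source that is not at hand, so one can only ask for its applicability to be checked.

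**Conclusion.** The point holds as a mismatch between a design input and the primary outcome. The calculation is correct for a control rate of 30/1000, but that is a regional rate and not the rate of facility-recorded deaths. The 80% power with 1065 per cluster is therefore not established for institutional neonatal mortality. Overstatement is the likely direction, because deaths at home after discharge drop out of the count while the facility birth stays in the denominator. Restriction to facility births and referral into hospitals work on the recorded rate too, and referral may raise it.

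The size cannot be fixed from the document. For assumed institutional rates of 28 down to 15 per 1000, power runs from 77–78% to 50–61% at 1065 per cluster, and from 80–81% to 53–65% at 1,221. These ranges assume a 30% relative reduction, equal clusters, the protocol's normal approximation, and either the stated ICC or its implied CV. The validity of the effect estimate is not affected. This should be fixed, but it does not undermine the trial.

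**What to change.** Recompute power, or the relative reduction detectable at 80% power, for the outcome that will be analysed. Use the baseline institutional neonatal death rate, its variation between the 16 districts (as an ICC or CV for that outcome), and the facility births expected over 18 months. Study design and Data collection already plan baseline figures on deliveries and on the primary outcome in both arms. The inputs should be baseline values and not the trial's own results, so that this does not become a post hoc power calculation.

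Replace the statement built on 30/1000, 1065 and 80% with the result, and say that the design rate is institutional. State also whether the cited ICC describes community or facility deaths.

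The cost is one recalculation and a rewritten paragraph, with a stated power that may be less favourable. No clusters, visits or data items are added. Recruitment was due to end in January 2017, so the use of the restated figure is in interpreting and reporting the result.
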